### Participant inclusion and exclusion criteria

Participants will be drawn from academic, professional and administrative employees at the University of Otago. To be eligible for inclusion, participants must (1) be older than 18 years; (2) self-report spending > 5 h per day, on at least 3 days of the week in a seated position at work (objectively measured sedentary time of participants who self-report being sedentary at work, has been reported to be 5.5 h [5]); and (3) not use a sit-to-stand desk. Part-time employees are eligible providing they meet the criteria above. Participants will be excluded from participating if (1) they have any physical or physiological impediments to participating in physical activity because this study requires participants to undertake short bouts of physical activity (all participants will be screened for contra-indications using the Physical Activity Readiness Questionnaire [PAR-Q] [24] prior to starting the study), (2) they have a planned absence from work for > 2 weeks during the intervention period, or (3) they plan to relocate to another workplace other than the University of Otago, Dunedin campus, during the 6 month study period (intervention and follow-up). Participants will also be excluded from participation if they are pregnant, as pregnancy has the potential to affect waist circumference, and other components of the cardio-metabolic risk score (a secondary outcome measure).

### Recruitment

Information about the study and copies of the recruitment flyers advertising the study will be emailed directly to contact points in all University Departments, and posted on campus related social media sites. Paper copies will be posted around the university campus and information on the study included in the Otago Bulletin Board (the University’s online newsletter). Individuals will either register their interest to participate by emailing the study investigators or will register directly on the link provided in the recruitment email.

### Sample size

From a feasibility study perspective, a formal sample size calculation is not required. However, for the pilot study component, one stated aim is to investigate changes in the number of opportunities to move taken over the work day (by comparing data from the pre-intervention to post-intervention periods) and the extent of participant adherence to the intervention. Consequently, using the standard deviation in the number of opportunities to move observed in previous research [5], our sample size calculation indicate that 47 participants from approximately 10 different offices will provide 90% power to detect a difference of three opportunities to move between pre-intervention and completion of the intervention or post-intervention periods to an alpha level of 0.05. This assumes that the within-person correlation in activity breaks is 0.5 and the standard deviation is 3. To account for office clusters a design effect of 4.2 was used (using an average cluster size of *n* = 5 and a strong ICC of 0.8). Allowing for a drop-out of rate of ~ 20%, 57 participants will be recruited. Having this stated sample size will also allow us to investigate the feasibility of achieving our target recruitment goal.

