### Measures

#### Feasibility: recruitment, retention, and acceptability

Successful recruitment will be defined as recruiting at least 57 participants over 1 month. Successful retention will be deemed as retaining 80% of participants who complete pre-intervention measurements (T1 and 2) through to the measurements taken at post-intervention follow-up (T4).

At the end of the intervention period (T3), semi-structured interviews will be held with participants, managers, and where possible, those who did not participate in the intervention but were working in close proximity to those that were. The purpose of the interviews is threefold. First is to ascertain why participants volunteered and their experiences of participating in the Move More @ Work intervention. Here, we will examine perceptions of how the intervention was delivered by the coach, the usefulness of the behaviour change components included in the intervention and the extent to which a supportive culture was created with respect to taking opportunities to move. We will also examine the acceptability of the data collection processes (wearing the accelerometers, blood collection, etc.). Second is to examine the impact of the intervention of those who did not actively participate. Third is to identify managers’ perspectives of employee participation in the intervention and perceptions of its strengths and weaknesses. These data will inform subsequent changes to the recruitment into, and delivery of, the intervention in any future trial. Participants who drop out of the intervention will be followed-up where possible to ascertain reasons for dropping out.

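### The recruitment target of 57 covers a 17.5% loss, not 20%, and the 90% power at 47 makes no small-sample allowance for about 10 offices

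*Protocol article*

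**What the plan says.** The Sample size section states that "47 participants from approximately 10 different offices will provide 90% power to detect a difference of three opportunities to move", comparing the pre-intervention period with the end of the intervention or the post-intervention period, "to an alpha level of 0.05". On variability: "This assumes that the within-person correlation in activity breaks is 0.5 and the standard deviation is 3". For clustering, "a design effect of 4.2 was used (using an average cluster size of" 5 "and a strong ICC of 0.8"). The last step is "Allowing for a drop-out of rate of ~ 20%, 57 participants will be recruited".

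The section names no formula, reference distribution or sidedness. It also says that the feasibility part needs no formal calculation.

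The figure 57 is used again. Under Feasibility: recruitment, retention, and acceptability, and in the criteria for a future effectiveness trial, 57 recruited within one month is the recruitment target. The retention target stands beside it: "Successful retention will be deemed as retaining 80% of participants who complete pre-intervention measurements", counted through to T4. The Data analysis section restricts the primary analyses to participants with data at T1, T2 and T3. The primary outcome is the change from the pre-intervention period, made up of T1 and T2.

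**The concern.** There are two separate issues.

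First, the drop-out allowance adds 20% of the completers instead of allowing for the loss of 20% of the recruits. The recruitment number therefore does not deliver the evaluable number when the stated loss occurs. It matters more than usual because 57 is also a progression criterion.

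Second, a design effect of 4.2 and about 10 offices leave very little independent information. A reference distribution that ignores this gives more power than an analysis whose precision comes mainly from the offices. A power figure stated without its basis may then be carried into planning of the next trial, which this pilot is meant to inform.

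**Working it through.** **Inputs (Sample size section):** difference 3; SD 3; within-person correlation 0.5; alpha 0.05, taken here as two-sided; average cluster size 5; ICC 0.8; about 10 offices; drop-out about 20%.

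**1. Reproducing 47**
- SD of change, one pre-measure and one post-measure: √(2 × 9 × (1 − 0.5)) = 3.0.
- Normal formula: n = ((1.960 + 1.282) × 3/3)² = 10.51, rounded up to 11.
- Design effect: 1 + (5 − 1) × 0.8 = 4.2.
- 11 × 4.2 = 46.2, rounded up to 47. The stated figure is reproduced.
- A noncentral t calculation with the same design effect and N − 1 degrees of freedom (df) also first reaches 90% at 47: 89.9% at 46 and 90.6% at 47. The text fits either route.

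**2. Drop-out step**
- 47 × 1.2 = 56.4, rounded up to 57. This is the plan's figure.
- Allowing for a 20% loss of recruits: 47/0.8 = 58.75, rounded up to 59.
- Loss that 57 can bear: 1 − 47/57 = 17.5%.
- A 20% loss from 57: 57 × 0.8 = 45.6, so 45 or 46 remain.

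**3. Power with a small-sample reference, one pre-measure (SD of change 3)**

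Effective size is N/4.2: 11.19 at 47 and 10.71 at 45. The noncentrality is (3/3) × √(effective size). The test is two-sided at 0.05.

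| Reference | 47 evaluable | 45 evaluable |
|---|---|---|
| Normal | 91.7% | 90.5% |
| t, N − 1 df | 90.6% | 89.3% |
| t, effective size − 1 df | 85.5% | 83.6% |
| t, 9 df (10 offices − 1) | 84.5% | 82.9% |

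With df taken from the effective size, 90% needs 13 effective observations (88.3% at 12, 91.1% at 13). That is 13 × 4.2 = 54.6, so 55 evaluable. As a sensitivity check, 47 people in 10 offices average 4.7 per office. The design effect is then 1 + 3.7 × 0.8 = 3.96, and power with 9 df is 86.5%.

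**4. Power on T3 minus the mean of T1 and T2**
- With correlation 0.5 between every pair of time points, the variance is 9 × (1 + (1 + 0.5)/2 − 2 × 0.5) = 6.75, so the SD is 2.60.
- With 9 df and the same design effect, power is 92.9% at 47 and 91.8% at 45.
- This is a plain difference in means. The model in the Data analysis section also fits time and an interaction, which this calculation leaves out.

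**The case against.** The strongest reply has four parts.

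**The 47 is not a miscalculation.** This stands. It follows from the stated inputs by a standard formula, and equally by a t calculation on N − 1 df. A reader might infer that the plan used a normal approximation and got its sum wrong. The document names no distribution, so neither inference is supported. The 84–85% depends on taking df from the effective size or the number of offices. That choice is well grounded when the plan itself assumes an ICC of 0.8 and about 10 offices, but it is this review's choice.

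**The drop-out gap is two people, and the text says about 20%.** This also stands as to size. By the normal formula, 45 evaluable still give 90.5%, so the slip alone does not bring power below 90% on that reading. On the N − 1 df reading it falls just below (89.9% at 46, 89.3% at 45).

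**The retention target does not settle the size of the primary analysis set.** It is tempting to say that meeting 80% retention leaves fewer than 47 for the primary analysis. The documents do not support that. The 80% runs to T4, whereas the primary analysis needs only T1, T2 and T3, and more people may have T3 data than T4 data.

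**Nothing in the pilot turns on power.** No progression criterion uses a p-value, and results are to be reported as mean changes with 95% confidence intervals. This limits the consequence. It does not make the two statements correct.

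**Conclusion.** The point holds in a limited form. The drop-out step is a definite slip that depends on no analytic choice: 57 allows a 17.5% loss, 59 would be needed for 20%, and a 20% loss leaves 45 or 46. The power statement is reproducible but optimistic for the contrast that its SD of change implies: about 84–85% at 47 and 83–84% at 45, given a two-sided test and a t reference on 9 to 10 df.

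A reader might conclude that the pilot is underpowered and must recruit more. That does not follow. With the mean of T1 and T2 as the pre-measure, which matches the description of the primary outcome, power is about 93% at 47 and 92% at 45 even with 9 df. That figure assumes a correlation of 0.5 between all time points and no time-trend term. The effect on the pilot's conclusions is small. What needs correcting is a stated power and a stated allowance for loss.

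**What to change.** Amend the Sample size section:

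- State that 57 recruits allow a 17.5% loss to 47, or a 20% loss to about 45.
- Restate the power with a named contrast and a small-sample reference based on the offices. Either give about 84–85% at 47 for one pre-measure against one post-measure, or give about 93% at 47 and 92% at 45 for T3 minus the mean of T1 and T2. For the second, state the assumptions of correlation 0.5 between all time points and no time-trend term.
- Mark the two-sided alpha and the choice of degrees of freedom as assumptions.

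The cost is a few sentences. The target of 57 and the progression criteria that use it can stay as they are.

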### Study procedures

#### Participant registration

Participants will confirm their interest in being involved in the study by registering online. A link will be sent to the participant to complete a questionnaire through REDCap, an online data capture system [25]. Here, participants will read the information sheet, provide consent, and then complete screening questions to assess eligibility. Participants can also request a paper copy to complete if preferred. Participants who do not meet the eligibility criteria will be informed of this and thanked for their interest. Those eligible will go on to provide demographic information (age, sex and ethnicity, marital status, level of education, work title, EFT employed, normal work hours), questionnaire-based outcome measures (e.g., psychological well-being, occupational fatigue, musculoskeletal health), and will be scheduled for an assessment session to complete the pre-intervention biophysical outcome measures.

#### Pre-intervention period

In this interrupted time series design, we will assess participants’ usual pattern of physical activity behaviour over a 4-week period prior to the intervention being introduced. We have identified this as the pre-intervention period and will assess accelerometer-measured physical activity after participants have registered for the study (T1) and 3 weeks later (T2). This essentially controls for any effects that may arise as a result of being in a study and any potential trends in physical activity across time. At the conclusion of this pre-intervention period, the intervention will be introduced.

### Move More @ Work intervention

The aim of this 12-week intervention is to encourage participants to perform 1–2 min of activity after every 30 min of continuous sitting throughout their workday. The intervention contains an individual behaviour change component delivered by a Move More @ Work Coach and a workplace culture component. The Behaviour Change Wheel [18] and the associated COM-B model and TDF were used in the design of the intervention along with research evidence of behaviour change strategies important to support reduction in sedentary behaviour [13] and our work investigating facilitators and barriers to performing regular activity breaks [15]. The specific intervention components and their mapping to the COM-B model and TDF are shown in Table 2.

**Table 2 Tab2:** Links between the COM-B model, TDF domains, intervention functions, and behaviour change techniques used in the Move More @ Work Intervention

COM-B model component and definition of the barrier/motivator influencing change		TDF domains	Intervention functions	Behaviour change techniques	Description of intervention strategy
Capability	*Psychological* A lack of knowledge of why prolonged sitting is harmful to health and benefits of incorporating regular movement.	*Knowledge* Increase knowledge of health risks to prolonged sitting (even when regularly physically active) and benefits of reduced sitting time. *Beliefs about consequences* Create expectancy that positive outcomes will occur with reduced sitting.	Education, persuasion	• Information on health consequences • Credible source	• Information on health consequences discussed by the Move More @ Work coach (MMWC) and in study booklet provided to participants.
	*Psychological* A lack of awareness of how sedentary the individual currently is.	*Knowledge* Increase awareness of how sedentary the individual currently is.	Education, persuasion	• Feedback on behaviour • Discrepancy between current behaviour and goal	• Participant booklet displays individualised pre-intervention activity patterns at work and expected behaviour during intervention. • Consultation with MMWC discusses discrepancy between current and expected behaviour and elicits participant’s feelings about discrepancy to encourage motivation to change.
	*Psychological/physical* A lack of understanding of what physical activities meet the criteria and how to perform them.	*Knowledge* Increase knowledge of what physical activities can be performed during an opportunity to move. *Skills* Develop skills necessary to perform required activities safely.	Education, training, persuasion	• Instruction on how to perform the behaviour and demonstration of the behaviour	• Examples of activities, and demonstration videos, that meet the requirements of an opportunity to move provided in study booklet. • MMWC demonstrates the behaviours during consultation.
	*Psychological* Lack of confidence in being able to perform regular opportunities to move.	*Beliefs about capabilities* Increase confidence in being able to change sedentary behaviour. *Goals* Create action plans. *Memory, attention, and decision processes* Enable decisions to move rather than be sedentary. *Behavioural regulation* Identify success through self-monitoring of behaviour.	Enablement, training, environmental restructuring	• Action planning • Problem solving • Prompt/cues • Self-monitoring of behaviour	• MMWC explains how to set action and barrier-coping plans. • Weekly email encourages participants to complete action and barrier-coping plans and to send a copy back to research team. • A reminder prompt set up on participant’s computer. • Participants provided with a daily checklist to tick off every time an opportunity to move is taken. This is returned to research team at the end of the week.
Opportunity	*Social* Perception that workplace culture created by managers is unsupportive of taking opportunities to move.	*Social influences* Create a workplace culture where managers are supportive of taking breaks.	Environmental restructuring, modelling	• Information about others’ approval • Restructuring the social environment • Social support (unspecified) • Identification of self as role model	• Support and encouragement for taking opportunities to move communicated at daily/weekly team meetings with manager. • Senior-managers endorse the study and encourage staff to take part through staff newsletters and email communications. • Managers encouraged to role model taking opportunities to move.
	*Social* Perception that colleagues would not be supportive of taking opportunities to move.	*Social influences* Create a social norm around taking opportunities to move.	Environmental restructuring	• Information about others’ approval • Restructuring the social environment	• Support and encouragement for taking opportunities to move communicated at daily/weekly team meetings with manager. • Staff display information on their desk stating, ‘I am taking an opportunity to move, I will be back in 2 min’.
	*Physical* Requirement for personalised support to enact change.	*Environmental context and resources* Provision of personalised support to develop required skills and abilities to take an opportunity to move.	Environmental restructuring, enablement	• Prompts/cues • Social support (Practical)	• A reminder prompt set up on participant’s computer. • Individualised plan created in meeting with MMWC.
Motivation	*Reflective* Overcoming perceptions that taking opportunities to move will decrease work productivity and not provide short-term benefits.	*Beliefs about consequences* Believing that taking breaks will not decrease productivity and will provide benefits. *Reinforcement* Recognising consequents of action will provide reinforcement for behaviour.	Education incentivisation, enablement	• Information on health consequences • Self-monitoring of outcomes of behaviour • Monitoring of emotional consequences	• Information presented by MMWC and in study booklet. • Participants asked to reflect at the end of each week about how they feel.
	*Reflective* Lack of motivation to perform the behaviour.	*Intentions* Create a conscious decision to change behaviour. *Goals* Create action plans to support intentions. *Behavioural regulation* Identify success through self-monitoring of behaviour.	Enablement	• Action planning • Problem solving • Self-monitoring of behaviour	• Weekly email encourages participants to complete action and barrier-coping plans and send a copy back to research team. • Participants provided with a daily checklist to tick off every time an opportunity to move is taken. This is returned to research team at the end of the week.
	*Automatic* Support to create a new habit and break old habits.	*Reinforcement* Create a new habit and routine.	Enablement	• Habit formation • Prompts/cues	• An opportunity to move is repeatedly taken following the reminder prompt set up on computer.

#### Move more @ work coach consultation

All participants will have an individual consultation with a Move More @ Work coach lasting around 30 min. The coach will undergo training on how to deliver the intervention components and to ensure that all elements are delivered as intended. Participants will be provided with a hard copy of a study booklet outlining the points discussed by the coach. Specifically, during this consultation, the coach will do as follows:
Briefly, discuss current evidence around sitting as a health hazard, and the health benefits associated with performing regular short bouts of movement throughout the day.Discuss and demonstrate where necessary, examples of physical activities that meet the intensity and duration required of an opportunity to move (for example, walking up and down stairs or along a corridor; repeatedly standing up from the chair and sitting back down; body weight resistance exercises such as squats, calf raises). Links to online videos demonstrating these specific movements will be provided in the study booklet.Discuss the participant’s profile of the time they spent sitting and being active at work collected from the pre-intervention accelerometer data. The coach will highlight the discrepancies between current sedentary time and the expected behaviour if participants take an opportunity to move every 30 min.Develop an individualised action and barrier-coping plan [26]. The action plan involves participants specifying exactly what activities they will perform (and would easily fit into their work context), when they will do them (e.g., may have different activities at different times of the day), and where (e.g., in the office, on the stairs). The barrier-coping plan involves participants identifying potential barriers that they may face when implementing this plan and putting strategies in place to overcome those barriers. A laminated card will be provided for the participant to record their action and barrier-coping plan each week. They will be encouraged to place this card within eyesight of their workstation to assist with self-monitoring.Provide participants with a laminated chart to record each opportunity to move that was performed each work day. At the end of each day, a section on the chart will prompt participants to self-reflect on how they are feeling.Discuss which external electronic prompt the participant would like to use as a reminder to take their opportunities to move (e.g., an outlook calendar reminder — available on a PC or Mac, or the computer announcing the time every 30 min — Mac only). The coach will then help the participant set these prompts up on their computer.

At the beginning of each week of the intervention period, participants will receive an email reminding them to set weekly action and barrier-coping plans. Participants will be asked to respond to the weekly email by sending back a copy of their action and barrier-coping plan to the research team (to indicate they have completed their plan). They will also be asked to email back a copy of the chart which detailed the number of opportunities to move performed on each day of the previous week.

